## Research design and methods

### Design

A randomized control design will be used to examine the impact of IY for youth aged 14-26 years with IBS on the following outcomes: IBS symptoms, global improvement, HRQOL, and laboratory pain sensitivity. The study design is depicted in Figure 2. After baseline assessment, including standardized questionnaires and the laboratory visceral task (including ANS/psychophysiological measurements and cortisol collection), participants will be randomly assigned to the IY program or the wait-list control group. It is anticipated that randomization will ensure equal distribution of males and females, adolescents and young adults, and symptom severity across groups. Baseline assessments will be completed in order to ensure that the yoga and control groups are comparable, and to test for pre/post changes in the yoga group.

**Figure 2 F2:**
[figure not shown]
**Flowchart of study design**.

#### Randomization

A research assistant who is not otherwise involved in the yoga study, and who has not met or had previous contact with any of the subjects, will use the Research Randomizer program as a means to generate random numbers (either 0 or 1) for patient assignment to the intervention or wait-list group. The program uses a JavaScript random number generator to produce customized sets of random numbers, which are then downloaded in an Excel database. Patients who have been screened and have entered the study will be listed in the recruitment database. This list of participants will be aligned with the output of random numbers. Patients with a number less than 0.5 will be assigned to the intervention group and those with a number greater than 0.5 will be assigned to the wait-list group. Consistent with the need to ensure allocation concealment [78], the randomization results will be kept in a secure, locked, password-protected Excel database that only the research assistant has access to.

Female participants will provide information on their last menstrual period during the baseline questionnaire and laboratory session, and where possible, their post-intervention questionnaire and laboratory session will be scheduled to take place during the same cycle phase as their baseline session (e.g., follicular vs. luteal phase). Pain may vary for women along with their menstrual cycle, both for laboratory pain tasks [79] and for general IBS symptoms [80]. It is therefore important to ensure that any change experienced by female patients after the IYP is not the result of completing the laboratory task during a more/less sensitive phase of their cycle.

Those initially assigned to IY will then engage in the 6-week biweekly program (each session will last 1.5 hours; total duration = 18 hours), while those assigned to the control group will receive care as usual. All participants will repeat the baseline assessments, including the sensitivity task and psychophysiological assessment and cortisol collection, immediately following the total treatment/control period. Questionnaires regarding symptoms will also be e-mailed at a 2-month post-treatment follow-up. Both the yoga and control groups will receive a weekly monitoring form to assess symptoms, physical activity, and lifestyle changes (and to ensure that the control group does not participate in any mind/body interventions that may impact findings). The weekly monitoring form will be administered by phone or e-mail to both groups at the end of each week. After the 6 weeks, controls will be re-assessed to ensure that they still meet study eligibility criteria; those who continue to meet criteria will take part in the IYP. Following IY, participants will repeat the baseline assessments at post-treatment and complete the 2-month post-treatment follow-up questionnaires.

According to the Power/Sample Size calculations outlined below, 30 patients in each of the intervention and control groups will be recruited (total n = 60). To accommodate this number, 4 IY groups and 4 initial control groups will be conducted, with approximately 8 patients per group.

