## Introduction

### The impact of IBS

IBS is a complex, chronic, functional disorder for which there is no cure. The condition is characterized by abdominal pain/discomfort and altered bowel habits; other symptoms may include nausea, vomiting, and bloating. IBS prevalence estimates in North America for adults and adolescents are between 10 -15% [1,2]. Boys and girls appear to be equally affected until late adolescence [3], when sex differences emerge and women are twice as likely to be affected as men [4]. Direct costs of IBS to the U.S. health system are in the region of $10 billion, with indirect costs contributing a further $20 billion [5]. IBS and related functional bowel disorders have been ranked as a common cause of illness-related absenteeism, second only to the common cold [6]. In addition to increased healthcare use and absenteeism, IBS has been related to an elevated risk of other somatic intestinal and extraintestinal comorbidities, psychological comorbidities such as anxiety and depression [7], and to reduced quality of life [8].

There are no definitive biochemical, structural or serologic markers to assist diagnosis or assessment of treatment efficacy [9]. Currently, symptom-based approaches are used in diagnosis and the Rome criteria, now Rome III [10], is the current gold standard of diagnostic tools. The Rome diagnostic criteria presume the absence of a structural or biochemical explanation for the symptoms, and diagnosis is made by an experienced clinician. ROME III criteria consist of recurrent abdominal pain or discomfort for at least 3 months, onset at least 6 months previously and with at least two of the following: improvement with defecation, onset associated with a change in frequency of stool, and/or onset associated with a change in appearance of stool. Sub-categories are based on stool consistency as IBS with constipation, IBS with diarrhea, or IBS with mixed or alternating constipation and diarrhea [11]. Criteria exist for both children (4-18 years of age) and adults (over 18 years of age).

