### Study participants

#### Enrollment criteria

Male and female youth will be eligible for the study if they meet the following criteria:

• Age 14-26 years.

• Diagnosis of IBS, using ROME III pediatric criteria for patients aged 14-17 years, and ROME III adult criteria for 18-26 year-olds.

• Able and willing to give written informed assent or consent and comply with the requirements of the study protocol.

• Ability to speak and understand English.

Every step will be taken to ensure that equal numbers of participants make up the sub-groups, including equal numbers of young men and women and young people across the entire age group studied.

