## Primary outcomes

### Questionnaires at baseline, post-treatment, and follow-up

**1**. ***IBS symptoms ***will be measured using the ***IBS severity scoring system (IBS-SSS) ***[88]. The scale measures the sum of the participant's evaluation on a 100-point scale of each of five items: severity of abdominal pain, frequency of abdominal pain, severity of abdominal distension, dissatisfaction with bowel habits, and interference with quality of life. The IBS-SSS has acceptable reliability and validity and is recommended for use in outcome studies [89]. It takes approximately 5 minutes to complete. Those younger than 18 will also receive the abdominal symptoms sub-scale of the Child Somatization Inventory (CSI). The CSI [90-93] measures perceptions of nonspecific somatic symptoms. Individuals rate how much they are bothered by each of 24 symptoms (e.g., headaches) during the last 2 weeks using a 5-point scale (*not at all *to *a whole lot*). It takes less than 5 minutes to complete.

**2. *IBS pain ***will be measured with the ***Abdominal Pain Index ***comprising five items assessing the frequency, duration and intensity of pain episodes over the previous 2 weeks. Good reliability and validity have been reported [94].

**3**. ***Global Improvement ***will be assessed with the ***Global Improvement Scale **(**GIS**)*. This scale asks participants "Compared to the way you felt before you entered the study, have your IBS symptoms over the past 7 days been from (1) = substantially worse, to (7) = substantially improved [95]". Global improvement is noted for patients endorsing moderately or substantially improved status. The scale shows adequate reliability and validity [95]. Global improvement, in addition to symptom severity, is recommended as a primary endpoint in IBS therapy trials [96]. The scale takes less than 1 minute to complete.

**4**. ***Health Related Quality of Life ***will be assessed with the ***Health Related Quality of Life - Short Form-36 (SF-36) ***[97] a generic core HRQOL measure yielding an 8-scale profile of functional health and well-being. The SF-36 performs well in an absolute sense and comparatively better than other HRQOL measures in terms of reliability, validity, and lightness of respondent/administrative burden [98]. It can be completed in 5-10 minutes and has been validated in children as young as 10 years of age [99].

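### Wait-list controls get yoga only if still eligible after week 6, which gives them, but not yoga participants, a possible reason to under-report improvement on the primary outcomes

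*Protocol article*

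**What the plan says.** The study flow is set out at the end of the Randomization section. Both arms repeat the baseline assessments "immediately following the total treatment/control period". A few sentences later the wait-list arm gets a further condition for entering the yoga programme: "After the 6 weeks, controls will be re-assessed to ensure that they still meet study eligibility criteria; those who continue to meet criteria will take". Yoga participants face no such condition.

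The Enrollment criteria include "Diagnosis of IBS, using ROME III pediatric criteria for patients aged 14-17 years, and ROME III adult criteria for 18-26 year-olds". The Introduction (The impact of IBS) says that no definitive biological marker exists, that "symptom-based approaches are used in diagnosis and the Rome criteria, now Rome III [10], is the current gold standard of diagnostic tools", and that an experienced clinician makes the diagnosis. It describes the content as follows: "ROME III criteria consist of recurrent abdominal pain or discomfort for at least 3 months, onset at least 6 months previously", together with features of defecation and stool.

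The primary outcomes (IBS-SSS, Abdominal Pain Index, Global Improvement Scale, SF-36) are all questionnaires that the participant completes. The global item asks about change outright: "Compared to the way you felt before you entered the study, have your IBS symptoms over the past 7 days been" worse or improved, on a seven-point scale. The Data analyses section sets 50 IBS-SSS points relative to controls as the clinically meaningful difference.

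**The concern.** Participants cannot be blinded to attending classes or waiting for them. The controls volunteered for a yoga trial, and their place in the classes depends on a re-check whose most changeable element is what they say about their symptoms. At about the same time they answer the primary questionnaires. A control who feels better but still wants the classes may prefer to give one consistent account in both places.

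The incentive exists in one arm only, and under-reported improvement among controls widens the yoga-minus-control difference at post-treatment. ANCOVA on baseline does not correct it, because the distortion arises after randomization and differs by arm. The estimate also has later uses. The Introduction makes superiority over wait-list the trigger for a follow-on trial, and the Significance section plans to size that work from the effect seen here.

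The protocol concedes in the Introduction that its control group leaves out social, attention and expectation effects. That caveat is about what a wait-list lacks. It does not mention this access rule, which a wait-list design does not need.

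**Working it through.** **1. What the text establishes**

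| Element | Where | Stated? |
|---|---|---|
| Controls' access depends on continued eligibility | Randomization | Yes |
| Eligibility includes a symptom-based diagnosis | Enrollment criteria; The impact of IBS | Yes |
| Primary outcomes are self-reported | Aims; Primary outcomes | Yes |
| Outcomes and re-check both follow the 6 weeks | Randomization | Yes |
| Which of the two comes first | – | No |
| Controls are told of the condition | – | No |
| A primary-outcome score governs access | – | No such cut-off |

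**2. How far real improvement could end eligibility.** The look-back described is at least 3 months, about 13 weeks. A window of that length ending at week 6 contains 6 weeks after baseline and about 13 − 6 = 7 weeks before it. More than half of it (7/13 ≈ 54%) lies before the control period, so genuine improvement over 6 weeks need not end eligibility. The article gives one definition and does not spell out the pediatric version, so for the 14-17-year-olds this assumes a similar look-back.

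**3. Numbers per arm.** The documents give no figure for reporting bias. The sample-size figure, which is not disputed here, supplies the arm size. With Cohen's f = 0.25 (taken as medium), two groups, two measurements, λ = f²·N·2/(1 − ρ) and df 1 and N − 2, 80% power needs N = 60 at ρ = 0.10 and N = 34 at ρ = 0.50, as stated. The midpoint is (60 + 34)/2 = 47, and 47/0.80 = 58.75, so 59 against the stated 60. After 20% attrition, 60 × 0.80 = 48, or 24 per arm.

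**4. Illustrative shift in the control mean (assumed inputs).** Shift = share of controls withholding × points withheld.
- Low: 0.10 × 50 = 5 points, and 5/50 = 10% of the threshold.
- High: 0.30 × 75 = 22.5 points, and 22.5/50 = 45% of the threshold.

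**5. Effect on the test if yoga had no true effect (assumed inputs).** Noncentrality = shift / [SD·√(1 − ρ²)·√(2/n)], two-sided 5%, df = 2n − 3, n = 24. SD is assumed to be 70 to 110 and ρ 0.3 to 0.5. Example with SD 90 and ρ 0.5: 90 × √0.75 = 77.9; 77.9 × √(2/24) = 22.5; 12.5/22.5 = 0.56, which gives a rejection probability of 8.5%.

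| Shift (points) | Rejection probability over the assumed range |
|---|---|
| 5 | 5.3–5.9% |
| 12.5 | 7–11% |
| 22.5 | 11–24% |

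**6. Global improvement (assumed inputs).** With 30 controls, every 3 who do not report being improved move the responder difference by 3/30 = 10 percentage points. If the true responder rate is 20 to 40% in both arms and a quarter to a half of improved controls deny it, the spurious difference runs from 0.20 × 0.25 = 5 to 0.40 × 0.50 = 20 percentage points.

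**The case against.** The strongest reply is that access does not depend on any outcome score. A control could report substantial improvement and a much lower IBS-SSS and still qualify. Most eligibility items (age, language, pregnancy, substance abuse, other disease) are not about symptoms, and re-checking some of them before treatment has a proper safety purpose. A clinician makes the diagnosis, and the look-back is long. The article does not say that controls know of the condition. It also does not fix the order of events: outcomes may already be collected first, and the flowchart and consent text are not available. Finally, the study calls itself preliminary and accepts the limits of a wait-list openly.

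Most of this stands, and it limits the point. A reader might infer that the rule does inflate the yoga effect, that improved controls will be shut out in numbers, or that access turns on the questionnaire scores. The documents support none of these. A reader might also infer that the bias leaves no trace. The weekly monitoring forms in both arms could show a jump in control scores at week 6, although they are self-reported too and so are only a partial check.

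The reply does not remove the incentive. It needs only that a control believes access depends on remaining symptomatic, and nothing in the text separates the re-check from the outcome answers. The long look-back also works against keeping the rule: a symptom re-check that few improved controls would fail does little for its purpose, yet can still influence what controls report.

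**Conclusion.** The point holds as a risk of bias. The plan attaches a symptom-related condition to yoga access in one arm only, at about the time of unblinded self-reported primary outcomes. Any resulting distortion favours yoga in the post-treatment comparison, and baseline adjustment does not remove it.

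Its size is unknown and cannot be derived from the documents. The 5 to 22.5 points, the rejection probabilities and the responder differences are illustrations that rest entirely on the assumed shares, points withheld, SD, correlation and responder rates. The conclusion also assumes that at least some controls know of the condition or believe in it. The sample size is unaffected. The severity is moderate: a cheap improvement, and not a defect that invalidates the trial.

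**What to change.** 1. Do not make controls' access to the yoga programme depend on symptom status at week 6.
2. Tell controls before baseline that their questionnaire answers do not affect access.
3. Complete and lock the week-6 primary outcomes before any re-check, and state that order in the protocol.
4. Limit the re-check to the non-symptom and safety eligibility items.
5. If a symptom re-check is wanted to define the second-round yoga cohort, use it only to decide who is analysed in that cohort, not who is offered classes.

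The cost is a change of wording in the protocol and participant information, a few additional class places, and a slightly more mixed second-round group.

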### Study participants

#### Enrollment criteria

Male and female youth will be eligible for the study if they meet the following criteria:

• Age 14-26 years.

• Diagnosis of IBS, using ROME III pediatric criteria for patients aged 14-17 years, and ROME III adult criteria for 18-26 year-olds.

• Able and willing to give written informed assent or consent and comply with the requirements of the study protocol.

• Ability to speak and understand English.

Every step will be taken to ensure that equal numbers of participants make up the sub-groups, including equal numbers of young men and women and young people across the entire age group studied.

#### Exclusion criteria

Patients will be excluded from the study based on the following criteria:

• History of drug, alcohol, or chemical abuse within 6 months prior to screening.

• Any other injury, disease, metabolic dysfunction, physical examination finding, or clinical laboratory finding giving reasonable suspicion that it might affect the interpretation of the results or render the patient at high risk from treatment complications.

• Inability to comply with study and follow-up procedures.

• Currently pregnant.

• Previous practice of IY within the past three months.

• Inability to speak and understand English.

• Plan to begin a new treatment within 2 weeks of the IYP.

Because a number of the outcome measures have been validated in English only and the IY protocol is only in English, for this initial study only those patients able to speak or understand English will be included. However, in future large-scale trials, Spanish speaking individuals will be included and we will translate and back-translate the questionnaires into Spanish if no Spanish versions exist, as well as develop yoga protocols that are in Spanish, and employ Spanish speaking IY teachers. We will ask participants whether they are pregnant at the time of study entry; however, the IY classes will not contain poses that are harmful to pregnant women. Substance/alcohol abuse, as well as practice of yoga, will be assessed via self-report. Although subjects will not be excluded if they begin new treatments during the IYP, those subjects who are planning on introducing new treatment 2 weeks or less before the IYP commences will be excluded. These patients will be offered participation in the next round of IY classes.

#### Recruitment

Participants will be recruited from the pediatric gastroenterology clinic and the UCLA Center for Neurobiology of Stress (CNS) in the Division of Nutrition and Digestive Disease at the David Geffen School of Medicine at UCLA, as well as from the UCLA Pediatric Pain Program (PPP) clinic, which sees patients up to 22 years of age. Recruitment will also occur at various medical offices specializing in digestive disturbances. Participants will also be recruited through community resources, such as library and other public notice boards, as well as websites of various IBS support groups and Craigslist. We will also recruit participants from press releases sent to surrounding areas through the UCLA Health Sciences Media Relations department. Figures at the UCLA Division of Digestive Diseases and the PPP suggest that approximately 15 IBS patients per month will be recruited in the appropriate age group. Private practice digestive specialists in Los Angeles who have agreed to refer to the project can refer an additional 18 patients with IBS per month in the targeted age range.

The study administrator will meet with health care providers, staff, and support group leaders to inform them about the project and ask them to distribute and post flyers about the study. The flyers will describe the project and ask interested volunteers to call in to establish their eligibility. Effort will be made to recruit the patient sample to be broadly representative of the general population of IBS patients in the targeted age range. Early epidemiological data examining the racial/ethnic composition of IBS in a Southern California Health Maintenance Organization (HMO) suggest that approximately 82% of patients will be White (non-Hispanic), 8% Hispanic, 3.5% African American and 1% Asian [81]. Adult women are twice as likely to be affected, and sex differences in IBS generally begin in late adolescence [81]. The study is therefore likely to have a greater number of female patients. Recruitment efforts will attempt to reflect the demographic composition of the Greater Los Angeles area which is estimated to be approximately 75% White, 13% Asian, 10% African-American, 1% American Indian/Alaska Native, and 1% Native Hawaiian/Other Pacific Islander.

### Intervention

#### Iyengar yoga program

The poses to be included in this intervention are based on the teachings of BKS Iyengar. They will include supine poses, passive backbends, standing poses, and supported inversions (e.g., Down Dog on Ropes with chair; Rope headstand; Chair backbend on two chairs; Chair shoulder stand; Chair Halasana; Setubandha Sravangasana on Bench; Viparita Karani; Supta Baddhakonasana; and Supta Pada Ghustasana). All will be done with props as needed. Young IBS patients will be taught an IY practice that is specifically designed to address their abdominal issues. The yoga poses will be done with the aid of props (blocks, bolsters, chairs, straps, and blankets) to reduce tension and strain, promote circulation, and reduce apprehension of pain. The practice will help bring awareness to habitual patterns of holding tension, as well as increase range of motion and strength. Students will learn to tolerate increased sensation without gripping and creating stress as they develop deeper states of relaxation and calm. The intervention will be conducted by an experienced IY teacher. At the end of the 6-week IYP, participants who ask for referrals to IY studios/teachers in the community will be given a list of referrals. Participants will be provided with props during week 3 to begin an informal home practice, if they wish. All home practice as well as post-IY classes will be monitored during the weekly monitoring form and at follow-up.

